## Abstract

**Background:**

The incidence of acute kidney injury (AKI) has been increasing over time and is associated with a high risk of short-term death. Previous studies on hospital-acquired AKI have important methodological limitations, especially their retrospective study designs and limited ability to control for potential confounding factors.

**Methods:**

The Assessment, Serial Evaluation, and Subsequent Sequelae of Acute Kidney Injury (ASSESS-AKI) Study was established to examine how a hospitalized episode of AKI independently affects the risk of chronic kidney disease development and progression, cardiovascular events, death, and other important patient-centered outcomes. This prospective study will enroll a cohort of 1100 adult participants with a broad range of AKI and matched hospitalized participants without AKI at three Clinical Research Centers, as well as 100 children undergoing cardiac surgery at three Clinical Research Centers. Participants will be followed for up to four years, and will undergo serial evaluation during the index hospitalization, at three months post-hospitalization, and at annual clinic visits, with telephone interviews occurring during the intervening six-month intervals. Biospecimens will be collected at each visit, along with information on lifestyle behaviors, quality of life and functional status, cognitive function, receipt of therapies, interim renal and cardiovascular events, electrocardiography and urinalysis.

**Conclusions:**

ASSESS-AKI will characterize the short-term and long-term natural history of AKI, evaluate the incremental utility of novel blood and urine biomarkers to refine the diagnosis and prognosis of AKI, and identify a subset of high-risk patients who could be targeted for future clinical trials to improve outcomes after AKI.

## Background

As currently defined, acute kidney injury (AKI) refers to a sudden decrease in kidney function as measured by changes in serum creatinine concentration and/or urine output. This phenomenon has been best studied among hospitalized patients and is associated with a high risk (>30%) of short-term mortality in severe cases [1]. The importance of AKI as a clinical and public health problem is underscored by recent studies showing a rising incidence in the U.S. over the past several decades [2,3].

The vast majority of published studies on AKI have focused primarily on clinical outcomes that occur during the index hospitalization complicated by AKI [4-8]. In 2005, the American Society of Nephrology Renal Research Report listed as a "critically important knowledge gap" studies addressing "long-term outcomes" after an episode of AKI [1]. Recently, several studies have attempted to examine the impact of hospital-acquired AKI on longer-term outcomes, including the risk of development and acceleration of chronic kidney disease (CKD), end-stage renal disease (ESRD), and death [9-14]. However, many existing studies have important methodological challenges that hamper their ability to determine the independent contribution of AKI to these outcomes. These include retrospective study designs, suboptimal quantification of severity of baseline CKD and severity of AKI, ascertainment of clinical outcomes based on data collected as part of routine clinical care and limited ascertainment of important confounding variables. Consequently, there has been a growing appreciation of the need to more rigorously address this question.

In 2007, the National Institute of Diabetes, Digestive and Kidney Diseases (NIDDK) released an Request For Applications (DK-07-009 "Ancillary Studies in the Natural History of Acute Kidney Injury") to create a multi-center research consortium to address these knowledge gaps by expanding our understanding of the natural history of patients suffering from AKI. The Assessment, Serial Evaluation and Subsequent Sequelae of Acute Kidney Injury (ASSSESS-AKI) Consortium was established in 2008 to compare prospectively differences in the occurrence of renal and cardiovascular outcomes and death within a diverse, matched cohort of patients with and without AKI. The overall goals of ASSESS-AKI are to:

• Establish a diverse prospective, parallel, matched cohort of adults and children with and without AKI.

• Characterize the short-term and long-term natural history of AKI based on current serum creatinine-based diagnostic criteria.

• Evaluate the incremental utility of novel blood and urine biomarkers to refine the diagnosis and prognosis of AKI.

• Develop a prognostic risk model that integrates patient characteristics and biomarkers to help inform providers and patients about the risks of adverse events after an episode of AKI.

• Identify the subset of high-risk patients who could be targeted for future interventional clinical trials to improve outcomes after an episode of AKI.

The ASSESS-AKI Study will leverage ongoing studies involving patients undergoing cardiac surgery or in the intensive care unit and expand the study population to include a more general hospitalized population to provide a broadly representative study of the natural history of AKI.

## Methods

### Study organization

The ASSESS-AKI Study consists of a Data Coordinating Center (Pennsylvania State University), three Clinical Research Center networks through Kaiser Permanente Northern California (Oakland, CA; San Francisco, CA; Walnut Creek, CA), Vanderbilt University (Nashville, TN), and the Translational Research Investigating Biomarker Endpoints in Acute Kidney Injury (TRIBE-AKI) network (New Haven, CT; Cincinnati, OH; London, Ontario; Montreal, Quebec). A central laboratory for analysis of core biochemistries is located at the University of Minnesota and an electrocardiography reading center is based at Wake Forest University (Figure 1). In addition, ASSESS-AKI includes an External Advisory Committee and NIDDK project scientists.

**Figure 1 F1:**
[figure not shown]
**Organizational structure for the ASSESS-AKI Study**. NIDDK = National Institute of Diabetes, Digestive and Kidney Diseases; DCC = Data Coordinating Center; CRC = Clinical Research Center network; and ECG = electrocardiography

The Institutional Review Boards of the Data Coordinating Center and participating Clinical Research Centers' institutions approved the study.

### Study design

ASSESS-AKI will employ a parallel, matched, prospective cohort design of adult participants with and without AKI. In addition, ASSESS-AKI will attempt to enroll and prospectively follow all eligible children undergoing cardiac surgery requiring cardiopulmonary bypass who are participants in the TRIBE-AKI Consortium study. The study will enroll 1200 participants (1100 adults, 100 children) with approximately 50% of adult participants having AKI and the remaining 50% representing matched adult participants without AKI. Scheduled follow-up visits for each participant will occur during the subsequent four years. Informed consent will be obtained in all patients in accordance with the principles of the Declaration of Helsinki.

### Clinical research center networks

Participating Clinical Research Center Networks have active research programs related to AKI and the consortium is leveraging their existing research expertise, resources and infrastructure to establish the prospective, multi-center ASSESS-AKI cohort.

#### Kaiser Permanente Northern California

Kaiser Permanente of Northern California in collaboration with the University of California, San Francisco has been conducting a series of NIDDK-sponsored (U01DK060902, R01DK067126, R01DK058411) longitudinal studies characterizing the epidemiology and outcomes of acute, chronic, and end-stage renal disease within Kaiser Permanente's large and diverse community-based population in the San Francisco and greater Bay area. Kaiser Permanente is one of the largest integrated health care delivery systems in the U.S and provides comprehensive care for >3.2 million members that are ethnically and socioeconomically diverse and highly representative of the northern California and statewide population. Kaiser delivers comprehensive inpatient and outpatient care to its members through 18 hospitals and >60 additional ambulatory medical offices and captures many aspects of its care through the use of its comprehensive clinical (e.g., inpatient and outpatient laboratory tests) and administrative (e.g., diagnoses, procedures, mortality) databases, which will be leveraged for ASSESS-AKI. The Kaiser Permanente Division of Research will lead recruitment and enrollment of participants hospitalized in medical and surgical wards as well as intensive care units (ICU) at three Kaiser Permanente Medical Centers located in Oakland, San Francisco and Walnut Creek.

#### Vanderbilt University

Vanderbilt University Medical Center (VUMC) is a large tertiary referral center serving the middle Tennessee area and surrounding region and provides comprehensive acute and critical care services. ASSESS-AKI investigators are primarily leveraging the ongoing National Heart, Lung and Blood Institute (NHLBI)-funded (U01HL081332)-sponsored Validation of Acute Lung Injury Biomarkers for Diagnosis (VALID) Study. VALID is a single-center, prospective study whose purpose is to develop and validate a panel of diagnostic and prognostic plasma and/or urine biomarkers in a diverse cohort of 2550 critically ill patients at high risk for developing ALI/ARDS as well as AKI [15]. All adult (≥18 years) patients admitted to one of four ICUs at VUMC who remained in the ICU at day 2 were eligible for enrollment. Patients are excluded if they experienced a cardiac arrest before enrollment, had transfer orders written or anticipated within 4 hours, died or were discharged within 48 hours of ICU admission, were admitted for uncomplicated overdose, were in the ICU for >3 days before enrollment, or who had chronic lung disease requiring oxygen supplementation or pulmonary fibrosis. Per parent study protocol, blood and urine samples are currently collected at study enrollment on ICU day 2 and subsequent sampling on ICU day 4. In addition to VALID subjects, VUMC investigators are recruiting additional subjects from the same VALID ICUs as well as neurologic and burn ICUs who meet inclusion criteria for VALID.

#### TRIBE-AKI

TRIBE-AKI is an ongoing prospective cohort study of more than 1800 adults and children sponsored by the NHLBI (R01HL085757) whose goal is to validate selected biomarkers for the diagnosis and risk stratification of AKI after cardiac surgery (coronary artery bypass and/or valvular repair or replacement). Patients are excluded if they had any of the following: pre-operative AKI (≥0.5 mg/dL increase in serum creatinine concentration from preadmission to initiation of cardiac surgery); pre-operative end-stage renal disease (serum creatinine level ≥4.5 mg/dL [400 μmol/L] receiving chronic dialysis or prior renal transplant), prior cardiac transplant or insertion of left ventricular assist device; receipt of nephrotoxic agents within 48 hours preceding cardiac surgery, or acute infective endocarditis. Pediatric participants are limited to those requiring cardiopulmonary bypass. TRIBE-AKI participants have comprehensive clinical data, blood and urine samples collected pre-operatively as well as from the first five post-operative days. ASSESS-AKI will include a subset of TRIBE-AKI sites: Yale University, London Health Sciences Center (Ontario), University of Cincinnati Children's Hospital, and Montreal Children's Hospital (Quebec).

### Cohort participants

The ASSESS-AKI Study will enroll a diverse group of adults (age 18 to 89 years) and children (age one month to 18 years) with and without AKI from participating Clinical Research Center networks.

#### Baseline kidney function

To participate, all patients must have an available baseline pre-admission serum creatinine value, which is then used to estimate glomerular filtration rate (eGFR). A baseline serum creatinine value is defined as the outpatient, non-emergency department test result nearest to the index hospitalization. For the Kaiser Permanente and VALID Clinical Research Centers, the nearest value between 7 and 365 days before admission will be used, while for the TRIBE-AKI Clinical Research Center, the baseline serum creatinine can be present between 1 and 365 days before surgery, provided the patient is undergoing elective surgery. The rationale for this approach is based on preliminary data from the three Clinical Research Center networks demonstrating that the vast majority of potentially eligible participants do not have more than two to three pre-admission serum creatinine values during this time frame and that the most recent value is more likely to reflect the subject's "baseline" kidney function before the index hospitalization. All serum creatinine results must be performed using an isotope dilution mass spectrometry (IDMS)-traceable serum creatinine assay.

#### Exclusion criteria

Exclusion criteria were selected to balance the goal of maximizing representativeness of the cohort, clinical accuracy of AKI, and feasibility in achieving the project goals. These criteria are detailed in Table 1. The data sources used to ascertain information on these criteria include electronic and paper medical records, other electronic databases, and patient interviews.

**Table 1 T1:** Inclusion and exclusion criteria for the ASSESS-AKI Study.

Inclusion criteria	Exclusion Criteria
Adult participants aged 18 years to 89 years.	Inability to provide informed or surrogate consent.
Children aged greater than one month to less than 18 years old at cohort entry.	Died prior to the three-month study visit.
Documented "baseline" serum creatinine defined as the outpatient, non-emergency department test value nearest to the index hospitalization within 7 and 365 days prior to admission using an IDMS-traceable serum creatinine assay.	Incarcerated, institutionalized, or otherwise unable to participate in the study within a home, community, or clinical setting.
In the TRIBE-AKI consortium, pre-operative serum creatinine results from an IDMS-traceable assay obtained within seven days before cardiac surgery can be used to define "baseline" kidney function for the subset of participants who are undergoing non-urgent cardiac surgery.	Enrolled in an active interventional study at the three-month in-person study visit.
For pediatric participants in TRIBE-AKI, a pre-operative serum creatinine concentration measured in the local hospital clinical laboratory among patients scheduled for elective cardiac surgery.	Actively pregnant or breastfeeding. Prior chronic hemodialysis, peritoneal dialysis (lasting ≥three months), or estimated GFR <15 ml/min/1.73 m2 not receiving renal replacement therapy. History of solid organ and/or hematopoietic cell transplants.
	Acute glomerulonephritis diagnosed clinically or by biopsy.
	Clinically significant urinary tract obstruction, confirmed by imaging.
	Hospitalization involving acute nephrectomy.
	History of multiple myeloma.
	Hepatorenal syndrome.
	Metastatic cancer or systemic cancer receiving active treatment.
	New York Heart Association Class IV heart failure prior to index admission.
	Predicted survival of 12 months or less as determined by the participant's treating physician or Clinical Research.
	Center Principal Investigator.
	AKI participants who remain hospitalized 90 or more days after the AKI episode.
	ESRD at the time of the three-month study visit.
	Unable to provide at least 1.5 mL of plasma for adults at the Inpatient visit.
	Unable to provide at least 3 mL of urine for adults at the Inpatient visit.
	Unable to provide at least 10 mL of blood for adults and 1 mL of blood for children at the three-month visit.

### Definition of AKI

We recognize the limitations of the most recently proposed definitions for AKI (i.e., RIFLE[16] and Acute Kidney Injury Network [AKIN][17]), which are based only on changes in serum creatinine concentration and/or urine output. However, despite enthusiasm for potentially more sensitive and specific novel serum and urine biomarkers,[18] to date, none have been sufficiently validated as better measures of AKI or of subsequent prognosis than serum creatinine-based AKI criteria. A major goal of ASSESS-AKI is to provide key insights into the prognostic value of novel AKI biomarkers. Therefore, AKI will be operationalized as follows which is anticipated to capture a broad spectrum of kidney injury. For adult participants, AKI will be defined as ≥50% relative increase and/or absolute increase ≥0.3 mg/dL (26 μmol/L) in peak inpatient serum creatinine compared with baseline outpatient serum creatinine. For pediatric participants, AKI will be defined as ≥50% relative increase in peak inpatient serum creatinine compared with baseline serum creatinine. We did not incorporate urine output criteria from the AKIN classification scheme because of concern about the systematic availability and quality of data about urine output, especially in non-ICU patients who are unlikely to have indwelling urinary catheters. Furthermore, incorporating the urine output criteria for AKIN might overly enrich our cohort for patients with pre-renal azotemia.

To enhance the likelihood of enrolling an adequate number of adult participants with more severe AKI, we have set an enrollment target of at least one third of AKI participants having ≥100% relative increase in serum creatinine. To increase the probability of having an adequate number of adult participants with AKI due to causes other than rapidly reversible pre-renal azotemia, we have set an enrollment target of at least one third of AKI participants who meet AKI criteria lasting ≥48 hours. These additional enrollment targets are not mutually exclusive, and we anticipate significant overlap in these pre-specified subgroups. Furthermore, study nephrologists at each participating site will review selected index hospitalization information to classify each enrolled AKI case into one of the following presumptive categories: acute tubular necrosis (ATN), pre-renal azotemia, and other/unknown.

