### Definition of absence of AKI

Subjects will be considered not to have AKI if they meet the following criteria. For adult participants, non-AKI status will be defined as having both <20% relative increase and an absolute increase ≤0.2 mg/dL (18 μmol/L) in peak inpatient serum creatinine compared with baseline outpatient serum creatinine. For pediatric participants, non-AKI status will be defined as <50% relative increase in peak inpatient serum creatinine compared with baseline serum creatinine.

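### The adult AKI rule requires no in-hospital change, so slow creatinine drift before admission in advanced CKD can be labelled AKI and carried into the CKD-progression comparison

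*Protocol article*

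**What the plan says.** The Background section describes the condition as an abrupt one: "acute kidney injury (AKI) refers to a sudden decrease in kidney function". The section Definition of AKI turns this into a rule for adults: "AKI will be defined as ≥50% relative increase and/or absolute increase ≥0.3 mg/dL", measured as the inpatient peak against the outpatient baseline.

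The baseline is set under Baseline kidney function. For Kaiser Permanente and VALID, "the nearest value between 7 and 365 days before admission will be used". For elective surgery at TRIBE-AKI the value "can be present between 1 and 365 days before surgery". The same section says that most potentially eligible participants "do not have more than two to three pre-admission serum creatinine values during this time frame".

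Controls must show "both <20% relative increase and an absolute increase ≤0.2 mg/dL" (Definition of absence of AKI). Each enrolled AKI case is then sorted by a study nephrologist into one of three categories: "acute tubular necrosis (ATN), pre-renal azotemia, and other/unknown". At least one third of AKI participants are to meet the criteria for 48 hours or longer. CKD progression is a fall in eGFR of at least 50% from baseline, or reaching Stage 5, in participants whose baseline eGFR is below 60.

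**The concern.** The rule asks how far the inpatient peak lies above an older outpatient value. It does not ask when the rise happened. A creatinine of 2.5 mg/dL nine months before admission and 2.8 on every hospital day meets it.

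Four features of the plan leave such a case in place:

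- The control definition bars the patient from the comparison group, so the two definitions sort patients partly by their prior rate of decline.
- A flat, raised value lasts longer than 48 hours, so the case helps fill a target meant to enrich for AKI other than rapidly reversible pre-renal azotemia.
- None of the three review categories says that no acute change occurred.
- Matching and the listed regressors use baseline eGFR, but neither the slope before admission nor the age of the baseline value.

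The study's aim is the independent effect of AKI on later kidney disease. A patient already in decline enters the AKI group with part of the 50% loss accrued and probably keeps declining. Some of the AKI group's excess progression could then have preceded the admission.

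**Working it through.** The article gives no figure for this point, so there is none to reproduce. The check applies its definitions to patients with no acute event.

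**1. The rule applied to a flat inpatient value.** Relative rise = 0.3 / baseline.

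| Baseline to inpatient (mg/dL) | Relative rise | AKI? | Eligible as control? |
|---|---|---|---|
| 1.5 to 1.8 | 20% | yes | no |
| 2.0 to 2.3 | 15% | yes | no |
| 2.5 to 2.8 | 12% | yes | no |
| 3.0 to 3.3 | 10% | yes | no |

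The inpatient change is 0.0 mg/dL in every row.

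**2. How much decline is needed.** Assume creatinine = 1.2 × (eGFR/60)^(−1/1.209), that is, 1.2 mg/dL at eGFR 60. A rise of 0.3 mg/dL then corresponds to these falls:

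- eGFR 22.5: creatinine 2.70 to 3.00, a fall of 22.5 × (1 − (2.70/3.00)^1.209) = 2.7 ml/min
- eGFR 37.5: creatinine 1.77 to 2.07, a fall of about 6.5 ml/min
- eGFR 52.5: creatinine 1.34 to 1.64, a fall of about 11.4 ml/min
- eGFR 75: creatinine 1.00 to 1.30, a fall of about 20 ml/min

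Only in advanced CKD is this a plausible slow decline within a year.

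**3. Age of the baseline.** The nearest of m values spread uniformly over days 7-365 (assumption) has mean age 7 + 358/(m+1): 186, 126 and 97 days for m = 1, 2, 3. The chance that it is over 180 days old is (185/358)^m: 52%, 27% and 14%.

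**4. Share of patients with no acute event who are labelled AKI.** The simulation used 500,000 records per cell, eGFR uniform within its category, no measurement error and constant inpatient creatinine. Assumed slopes were mean −2/−3/−4 with SD 3/4/5 ml/min/year. Each cell gives the three slope scenarios in that order.

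| Baseline eGFR | One value | Nearest of two | Nearest of three |
|---|---|---|---|
| 15-29 | 17 / 27 / 34% | 9 / 16 / 22% | 6 / 11 / 16% |
| 30-44 | 1.6 / 5.2 / 9.9% | 0.45 / 1.9 / 4.1% | 0.2 / 0.8 / 2.0% |
| 45-59 | 0.0 / 0.3 / 1.4% | at most 0.35% | at most 0.1% |
| 60-89 | at most 0.03% | about 0% | about 0% |

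**5. How the labelled patients differ.** At eGFR 30-44 in the middle scenario, mean slope in those labelled AKI against those labelled non-AKI is −9.3 against −2.3 with one value, −9.9 against −2.7 with two, and about −10.4 against −2.8 with three. A more recent baseline makes such cases rarer but does not narrow the contrast.

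**6. Head start on the outcome.** If eGFR varies as creatinine to the power −1 to −1.2, a drift from 2.0 to 2.3 mg/dL is already a fall of 13-16%, counted toward the 50% threshold.

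**7. Translation to a relative risk, for scale only.** If AKI has no effect, spurious RR = 1 + f(k − 1). Here f is the share of drift cases in the AKI group being compared, and k is their risk relative to controls. Both are assumed. With k = 2-3, f = 5% gives 1.05-1.10, f = 10% gives 1.10-1.20 and f = 20% gives 1.20-1.40. The smallest relative risk that the article says it can detect is 1.35.

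**The case against.** The strongest objections concern size and scope, and most of them stand.

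- **Baseline age.** The plan uses the nearest value. Drawing one baseline uniformly over the year gives the upper end of the range, not the expected case. This stands, and the table shows the effect.
- **Denominator.** The tabulated percentages are shares of patients without an acute event, not shares of enrolled AKI cases. This stands. A reader might also take from the same simulation that about 100% of those labelled AKI against 30% of controls progress over four years at eGFR 30-44. That contrast sets pure drift cases against controls and follows largely from carrying straight-line slopes forward. It is not an estimate of bias in the AKI group.
- **Scope.** TRIBE-AKI may use elective pre-operative values only days old. At least one third of AKI cases are targeted to have a rise of 100% or more, which drift does not plausibly produce. Both points stand.
- **No time element at all.** A reader might infer this, but it goes too far. The peak must fall within the index admission, and specimens and the three-month visit are timed from the AKI episode. The full protocol may hold an onset rule. The operational definition printed in the article still requires no acute change.
- **Acknowledgement and adjudication.** The Discussion concedes that baseline values may not reflect steady state, and describes urine microscopy and standardized case adjudication. It lists the first among recruitment barriers and gives no correction. The second serves to assign AKI type, and no category removes a case.
- **Harm from exclusion.** Removing cases that have not recovered by month 3 would also remove true AKI that peaked by admission and did not resolve. It would select exposure on an early part of the renal outcome. This stands and limits the remedy.

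**Conclusion.** The point holds in a limited form. Read together, the adult AKI rule, the baseline window and the control rule label flat, chronically raised creatinine in advanced CKD as AKI, and no stated safeguard identifies these cases. The exposed outcome is CKD progression, mainly at baseline eGFR 15-44 outside TRIBE-AKI participants with a recent pre-operative baseline. Incident CKD is essentially unaffected, because at eGFR 60-89 at most 0.03% would be mislabelled.

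Among patients with no acute event, about 6-34% at eGFR 15-29 and about 0.2-10% at 30-44 would be labelled AKI. These ranges rest on the assumed slopes, the creatinine-eGFR relation and uniformly spread baseline tests. A reader might infer that an observed link between AKI and CKD progression would be an artefact of the definition. The article does not support that, because it gives neither the share of such cases among enrolled AKI participants nor their risk, and the total bias cannot be derived from it.

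**What to change.** - **Flag.** In the planned nephrologist review, mark AKI cases with no documented acute change: no rise of at least 0.3 mg/dL or at least 50% above the lowest inpatient value, and no fall during the admission. State in advance how large a fall counts. Do not use month-3 creatinine to define the flag.
- **Target.** Do not count flagged cases toward the 48-hour target.
- **Primary analysis.** Keep the AKI definition as it is.
- **Sensitivity analyses.** Pre-specify an analysis of CKD progression in participants with baseline eGFR below 60 that omits flagged cases and their matched controls. Separately, adjust for or restrict on the age of the baseline creatinine.

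The cost is a little more review work, using serial inpatient creatinines that the peak and 48-hour criteria already need, and fewer cases in the sensitivity analysis. Some true AKI that peaked by admission and did not recover will be flagged, so the flag should not become an exclusion from the primary analysis.
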